### **10.3 Other study parameters**

Not applicable.

### **10.4 Interim analysis (if applicable)**

No interim analysis will be carried out since this study has a follow-up of only one year.

## 11. ETHICAL CONSIDERATIONS

### 11.1 Regulation statement

This study will be conducted according to the principles of the Declaration of Helsinki (Version October 2013, adopted at the 64th WMA General Assembly, Fortaleza, Brazil) and in accordance with the Medical Research Involving Human Subjects Act (WMO).

### 11.2 Recruitment and consent

#### Practices

This study will be embedded in the Academic Network of General Practices of the VU Medical Center (ANH-VUmc, [www.anh-vumc.nl](http://www.anh-vumc.nl)) and the General Practitioners Cooperative Twente (Twentse huisartsenonderneming Oost Nederland, [www.thoon.org](http://www.thoon.org)). After randomisation, all GP's in the participating practices will be informed about the outcome (intervention practice or control practice) of the randomisation. At this point the GP's will also receive extra information about the study and instructions for the GPs, specified to the situation of the practice (intervention or control practice). The following care professionals will be invited for trainings: pharmacists who will participate in group meetings for FRID-analysis; physiotherapists for the physiotherapy intervention; and POH-GGZs and psychologists who will participate in the stepped-care program.

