### 4.3 Exclusion criteria

A potential subject who meets any of the following criteria will be excluded from participation in this study:

- severe cognitive impairment according to the patient's GP
- serious co morbidity that precludes participation in an exercise program
- current enrolment in interfering study
- if the patient's GP deems participation of the patient in this study undesirable and/or if participation could damage the doctor-patient relationship for any reason. The GP's judgement in relation to possible damage of the doctor-patient relationship will always overrule other in- or exclusion criteria.

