### 8.2 Randomisation, blinding and treatment allocation

Randomisation will take place at practice level. Randomisation will be executed by a researcher who is not involved in the selection of the practices (concealment of allocation). Practices will be randomly assigned to intervention practice or control practice. Stratification will take place for practice type (solo or group practice) and area (practice in disadvantaged areas or not) and block randomization will be used to create similar distributions in the different study arms. Randomisation of practices will be executed before inclusion of patients.

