#### Recruitment of patients

Patients will be recruited via two routes: through identification of patients by the GPs and via searches in the electronic medical databases (EMD) of the GPs. We will use the strategy of identification of patients by the GP since this has been proven to be successful in the DIEP study. In addition to this we will ask the GP's to do a search in their EMDs every three months to make sure we will not miss eligible patients.

Identification of patients by the GPs will take place during consultation hours. If a GP sees an eligible patient for this study, the GP will inform the patient about the presence of the study and will ask for the patients' permission to be approached by the researcher. If the patient has given his/her permission, the GP will register the obtained permission in the EMD and inform the researcher (by fax or e-mail) about the patient's name and address. The researcher will then send the patient an invitation letter.

Secondly, the GP will be asked to execute a search in his/her EMD every three months. The GP will exclude all identified dizzy patients that fulfil the exclusion criteria. The researcher will then check which patients have not yet been invited to participate in the

study. Patients identified through searches in the EMD will receive an invitation letter on behalf of their GP.

Additionally to the invitation letter, all patients will receive a brochure with study information, a contact form and the DHI-S. Patients will be asked to fill out the DHI-S if they want to participate in the study. All patients with a DHI-S of  $\geq 12$  will receive a phone call of the researcher to set an appointment for baseline assessment at the patients home. Patients with a DHI-S score of  $< 12$  are not eligible to participate in the study.

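### GPs know their practice's arm when they identify, filter and may exclude patients, and no masking of the baseline assessor is described, so groups B and C can differ at entry

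*Protocol*

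**What the plan says.** - **Unit and order of allocation.** Section 8.2 states "Randomisation will take place at practice level" and "Randomisation of practices will be executed before inclusion of patients".
- **Concealment.** The only statement is in section 8.2: "Randomisation will be executed by a researcher who is not involved in the selection of the practices (concealment of allocation". It concerns the choice of practices.
- **Disclosure.** Under Practices, section 11.2 says that after randomisation "all GP's in the participating practices will be informed about the outcome (intervention practice or control practice) of the randomisation". At the same point GPs receive "instructions for the GPs, specified to the situation of the practice (intervention or control practice".
- **Patient entry.** Section 11.2 (Recruitment of patients) has two routes. In the first, "Identification of patients by the GPs will take place during consultation hours". In the second, the GP searches the EMD every three months, and "The GP will exclude all identified dizzy patients that fulfil the exclusion criteria". The researcher then checks which of the remaining patients have not yet been invited.
- **Discretion.** Section 4.3 lets the GP exclude a patient whenever the GP regards taking part as undesirable, and adds: "The GP's judgement in relation to possible damage of the doctor-patient relationship will always overrule other in- or exclusion criteria".
- **Risk label.** Section 3 puts a patient in B or C, rather than A, if the DHI is at least 30 and one or more of three factors is present: three or more fall-risk-increasing drugs, anxiety/depression, or impaired mobility. Section 8.3 gives the interview and timed walk to a physician or trained research assistant. Section 5.1 has the researcher resolve discrepancies in the drug list.
- **Blinding.** The heading of section 8.2 includes the word, but the text beneath it says nothing on the subject.

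**The concern.** In a cluster trial, concealing the sequence from whoever selects the practices secures comparable practices. It does not secure comparable patients if patients are found and filtered later by people who know the arm. Here those people also have different reasons, by arm, to enter someone. An intervention practice takes on a medication consultation with a feedback form and nurse-led stepped care, whereas a control practice gives usual care. A GP may, without intending it, put forward different patients in the two arms.

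At stake is the B versus C comparison of one-year DHI change. Differences at entry in frailty, severity or motivation would add to, or subtract from, the intervention effect. Recruiting more patients does not reduce a bias of this kind. Adjustment deals only with what is measured and put in the model.

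**Working it through.** **1. Order of events**

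1. Practices are randomised (8.2).
2. GPs learn their arm and receive arm-specific instructions (11.2, Practices). The protocol gives no date for this step. It follows randomisation directly and carries the instructions GPs need to take part, so it comes before they recruit.
3. GPs identify patients in consultation and filter the EMD search (11.2, Recruitment of patients), using the exclusions in 4.3.
4. Patients return the short DHI and contact form. Consent and baseline assessment follow (11.2, 8.3).
5. The A versus B/C label is set (3).

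Every patient-level decision comes after step 2. The concealment in 8.2 ends at step 1.

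**2. Where knowledge of the arm could act**

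- *Identification in consultation:* the informed GP decides whom to mention the study to.
- *EMD filter:* the informed GP applies the exclusions. The researcher's check covers only those who remain.
- *Discretionary exclusion:* it is open-ended, and no log is required.
- *Risk label:* the DHI and the anxiety/depression factor are scored from questionnaires. The drug factor comes from interview and pharmacy list, reconciled by the researcher. The mobility factor is a timed walk with a 20-second cut-off. An assessor has most room in the walk and some in the drug count.

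**3. Scale of the trial, as context**

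The inputs from section 4.4 are SD 19.9, target 12 points, z-values 2.58 and 1.28, cluster size 5, ICC 0.05 and loss to follow-up 20%.

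- n = 2 × (2.58 + 1.28)² × 19.9² / 12² = 81.9, so 82 per arm, as stated. (The worked expression prints 1.64, which would give 98; that is a separate matter.)
- Design effect = 1 + (5 − 1) × 0.05 = 1.2, and 82 × 1.2 = 98.4, so 99.
- 99 / 0.8 = 123.75, so 124 per arm, or 248 in total, stated as 250.
- SE of the B–C difference with 99 analysed per arm = 19.9 × √(2 × 1.2 / 99) = 3.10 DHI points.

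**4. Illustration (assumed shifts)**

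The protocol gives no size for an entry imbalance. Let b be the shift in the B–C difference that remains after adjustment, assumed to be 2, 4 or 6 points.

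- Type I error = 1 − Φ(2.58 − b/SE) + Φ(−2.58 − b/SE), for a shift in favour of the intervention with no true effect.
- Power = Φ((12 − b)/SE − 2.58), for a shift against the intervention with a true effect of 12.

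| Assumed b | b/SE | Type I error (nominal 1%) | Power (90% at b = 0) |
|---|---|---|---|
| 2 | 0.65 | 2.7% | 74% |
| 4 | 1.29 | 9.9% | 50% |
| 6 | 1.94 | 26% | 26% |

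The table shows how sensitive the test is to such a shift. It does not estimate the shift in this trial.

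**The case against.** **Safeguards in the protocol.** Several reduce the risk. The EMD search is there so that eligible patients are not missed. The entry cut-offs are fixed. The DHI and the anxiety/depression scores are patient-reported. A pharmacy list backs the drug count, and the walk has a standard procedure with a practice run. By the estimates in section 5.1, 62% of the intervention group would qualify for medication adjustment and 48% for stepped care, against 37% for exercise therapy, so the factor most open to the assessor applies to the smallest share. Section 10.1 plans an adjusted model. All of this stands, but the informed GP still filters the search, and adjustment cannot reach unmeasured traits.

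**Stronger readings.** A reader might infer four things that the protocol does not support:

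- *That the concealment claim is false.* It is worded for the selection of practices and is correct in that scope.
- *That assessors know the arm.* The protocol is silent. It neither says that they know nor requires that they do not.
- *That a particular bias in DHI points can be stated.* Any figure built on a baseline DHI imbalance rests on an assumed imbalance. Baseline DHI is measured, and adjusting for it would remove that component.
- *That the comorbidity exclusion operates only in intervention practices.* Section 4.3 applies it to every potential subject. A difference in how GPs use it is possible but is an inference.

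**GP identification.** It may also be argued that this route should stay, because section 11.2 justifies it by success in the earlier cohort study. That is accepted. Relying on the search alone could also delay contact by up to three months.

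**Conclusion.** The point holds as a risk created by the stated procedure. Followed exactly, the plan has GPs who know their arm identifying, filtering and excluding patients with open discretion, and it does not require the baseline assessor to be unaware of the arm. Groups B and C can differ at entry; it is not shown that they will. Neither the size nor the direction is known. The figures in the table depend entirely on the assumed residual shifts of 2 to 6 points and on the protocol's own SD, ICC and cluster size.

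This is a matter of trial conduct that the protocol itself fixes, and it cannot be left to an analysis plan. It is a worthwhile, inexpensive improvement. It does not make the design invalid, since telling GPs their arm may be unavoidable with this intervention.

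**What to change.** 1. **Recruitment (11.2).** Keep both routes. Run the three-monthly EMD search with one code list and one time window in both arms, as a common check list. Invite every patient found who does not meet a listed exclusion. The GP's discretionary exclusion stays available, but each use is logged with its reason. Numbers identified, excluded and labelled high risk can then be compared by arm.
2. **Baseline assessment (8.2 and 8.3).** Require that whoever does the timed walk, the interview and the drug-count reconciliation is not told the practice's arm until the A versus B/C label is locked.

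The search and the assessment already exist, so a short amendment is enough. The cost is a brief GP log and some coordination to keep the assessor unaware of the arm, which may occasionally fail if a patient reveals it. The changes reduce selective entry and make it visible, but they do not remove it, because GPs still know their arm.

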#### Recruitment of patients

Patients will be recruited via two routes: through identification of patients by the GPs and via searches in the electronic medical databases (EMD) of the GPs. We will use the strategy of identification of patients by the GP since this has been proven to be successful in the DIEP study. In addition to this we will ask the GP's to do a search in their EMDs every three months to make sure we will not miss eligible patients.

Identification of patients by the GPs will take place during consultation hours. If a GP sees an eligible patient for this study, the GP will inform the patient about the presence of the study and will ask for the patients' permission to be approached by the researcher. If the patient has given his/her permission, the GP will register the obtained permission in the EMD and inform the researcher (by fax or e-mail) about the patient's name and address. The researcher will then send the patient an invitation letter.

Secondly, the GP will be asked to execute a search in his/her EMD every three months. The GP will exclude all identified dizzy patients that fulfil the exclusion criteria. The researcher will then check which patients have not yet been invited to participate in the

study. Patients identified through searches in the EMD will receive an invitation letter on behalf of their GP.

Additionally to the invitation letter, all patients will receive a brochure with study information, a contact form and the DHI-S. Patients will be asked to fill out the DHI-S if they want to participate in the study. All patients with a DHI-S of  $\geq 12$  will receive a phone call of the researcher to set an appointment for baseline assessment at the patients home. Patients with a DHI-S score of  $< 12$  are not eligible to participate in the study.

### Consent

Informed consent will be obtained in two steps; by a contact form and an informed consent form. Firstly, the patient receives contact form together with the invitation letter. If the patient decides to be willing to participate in the study then he/she will sign the contact form. By signing the contact form, the patient gives permission to be approached by the researcher.

About two weeks later, before the start of the baseline assessment at the patients home, the informed consent procedure including signing of the informed consent form will take place. The patient has had sufficient time to think about participating in the study at this point and there is room for the patient to ask questions to the researcher or research assistant. By signing the informed consent form, the patient agrees to participate in the study.

### **11.3 Objection by minors or incapacitated subjects (if applicable)**

Not applicable.

### **11.4 Benefits and risks assessment, group relatedness**

This study aims to provide GPs with an easy-to-use clinical tool to identify dizzy older patients with a poor functional prognosis. The identification of dizzy elderly with a poor functional prognosis will enable the GP to provide better care to these patients. Furthermore the investigation of the effectiveness of a risk factor guided intervention for dizzy older patients might result in less impairment due to dizziness and/or a decrease in dizziness frequency in older patients.

To assess the clinical tool, the effectiveness of the intervention and the cost-effectiveness of the intervention it is necessary to collect data via baseline assessment and questionnaires.

There are no major medical health risks for participants in this study. The experimental group might benefit from their extra therapy by possibly resulting in less impairment due to dizziness and/or a decrease in dizziness frequency.

### **11.5 Compensation for injury**

The sponsor/investigator has a liability insurance which is in accordance with article 7, subsection 9 of the WMO.

The sponsor (also) has an insurance which is in accordance with the legal requirements in the Netherlands (Article 7 WMO and the Measure regarding Compulsory Insurance for Clinical Research in Humans of 23th June 2003). This insurance provides cover for damage to research subjects through injury or death caused by the study.

1. € 450.000,-- (i.e. four hundred and fifty thousand Euro) for death or injury for each subject who participates in the Research;
2. € 3.500.000,-- (i.e. three million five hundred thousand Euro) for death or injury for all subjects who participate in the Research;
3. € 5.000.000,-- (i.e. five million Euro) for the total damage incurred by the organisation for all damage disclosed by scientific research for the Sponsor as 'verrichter' in the meaning of said Act in each year of insurance coverage.

The insurance applies to the damage that becomes apparent during the study or within 4 years after the end of the study.

### **11.6 Incentives**

Not applicable.

## **12. ADMINISTRATIVE ASPECTS, MONITORING AND PUBLICATION**

### **12.1 Handling and storage of data and documents**

Information from questionnaires will be inserted in a structural database. During baseline assessment all data will immediately be registered in Blaise, a software programme for standardized data registration that helps to avoid the occurrence of missing data. Data from Blaise can be extracted and collected in the structural database later. We will use subject identification numbers and the key to the code of the subject identification number is safeguarded by the principal investigator. Only the principal investigator and the research assistants will have access to the source data. Data will be kept for as long as the study takes, and at least 5 years.

### **12.2 Monitoring and Quality Assurance**

An independent monitor from the Clinical Research Bureau (CRB) of VUmc will have access to the data and source documents of the trial. Monitoring will be performed in compliance with Good Clinical Practice (GCP) and other rules and regulations in order to achieve high quality research and secure patient safety. Detailed monitoring procedures will be described by the CRB in a study-specific monitoring plan.

### **12.3 Amendments**

Amendments are changes made to the research after a favourable opinion by the accredited METC has been given. All amendments will be notified to the METC that gave a favourable opinion.

### **12.4 Annual progress report**

The sponsor/investigator will submit a summary of the progress of the trial to the accredited METC once a year. Information will be provided on the date of inclusion of the first subject, numbers of subjects included and numbers of subjects that have completed the trial, serious adverse events/ serious adverse reactions, other problems, and amendments.

### **12.5 End of study report**

The investigator will notify the accredited METC of the end of the study within a period of 8 weeks. The end of the study is defined as the last patient's last visit.

In case the study is ended prematurely, the investigator will notify the accredited METC within 15 days, including the reasons for the premature termination.

Within one year after the end of the study, the investigator/sponsor will submit a final study report with the results of the study, including any publications/abstracts of the study, to the accredited METC.

#### **12.6 Public disclosure and publication policy**

The results of research will be submitted for publication to peer-reviewed scientific journals. There are no restrictions placed upon publication by the sponsor of this study (*ZonMw, programma Kwaliteit van Zorg: Versnellen, verbreden, vernieuwen*).

### **13. STRUCTURED RISK ANALYSIS**

Not applicable.

